## Abstract

**Background:**

Studies have shown that lifestyle interventions are effective in preventing or delaying the onset of type 2 diabetes in high-risk patients. However, research on the effectiveness of lifestyle interventions in high-risk immigrant populations with different cultural and socioeconomic backgrounds is scarce. The aim was to design a culturally adapted lifestyle intervention for an immigrant population and to evaluate its effectiveness and cost-effectiveness.

**Methods/design:**

In this randomized controlled trial, 308 participants (born in Iraq, living in Malmö, Sweden and at high risk of type 2 diabetes) will be allocated to either a culturally adapted intervention or a control group. The intervention will consist of 10 group counseling sessions focusing on diet, physical activity and behavioral change over 6 months, and the offer of exercise sessions. Cultural adaptation includes gender-specific exercise sessions, and counseling by a health coach community member. The control group will receive the information about healthy lifestyle habits provided by the primary health care center. The primary outcome is change in fasting glucose level. Secondary outcomes are changes in body mass index, insulin sensitivity, physical activity, food habits and health-related quality of life. Measurements will be taken at baseline, after 3 and 6 months. Data will be analyzed by the intention-to-treat approach. The cost-effectiveness during the trial period and over the longer term will be assessed by simulation modeling from patient, health care and societal perspectives.

**Discussion:**

This study will provide a basis to measure the effectiveness of a lifestyle intervention designed for immigrants from the Middle East in terms of improvement in glucose metabolism, and will also assess its cost-effectiveness. Results from this trial may help health care providers and policy makers to adapt and implement lifestyle interventions suitable for this population group that can be conducted in the community.

**Trial registration:**

ClinicalTrials.gov, NCT01420198

## Background

Type 2 diabetes (T2D), impaired fasting glucose (IFG), impaired glucose tolerance (IGT) and impaired glucose regulation (IGR) are among the strongest risk factors for cardiovascular disease (CVD) and death [1,2]. The prevalence of T2D is increasing, and it is estimated that by 2025, 15% of the global population will be affected by T2D, IFG or IGT [3]. The increase is thought to be due to population growth, ageing, urbanization, physical inactivity and obesity [4].

Immigrants from the Middle East and their offspring living in Sweden are at particularly high risk of T2D [5,6]. Malmö is a multicultural Swedish city. 30% of its residents were born abroad and the largest immigrant group consists of individuals born in Iraq, who collectively comprise almost 9,000 of Malmö’s nearly 300,000 inhabitants. In 2010, a pilot survey of almost 200 residents of Rosengård in Malmö who were born in Iraq or Sweden revealed a very high prevalence of T2D (20%), independent of country of birth, perhaps as a result of the study having been conducted in a socioeconomically vulnerable area [7]. Since January 2011, the MEDIM (the impact of Migration and Ethnicity on Diabetes In Malmö) project has continuously recruited residents with Iraqi and Swedish backgrounds aged 30 to 75 years from the whole of Malmö. Preliminary results obtained by June 2012 show that the prevalence of T2D is twice as high in Iraqi immigrants (n = 898) compared to Swedish participants (n = 757) (12.4% vs. 5.9%, p < 0.001), and that risk factors for T2D, such as family history of diabetes (52%), physical inactivity (64%) and obesity (38%), cluster in Iraqi subjects (manuscript submitted November 2012).

A previous study indicated that patients with T2D from the Middle East have a different form of T2D, with earlier onset and stronger family history function [8]. Furthermore, the same study indicated that immigrants from the Middle East have a more rapid decline in pancreatic beta-cell function compared to Swedish diabetic patients [8]. It is known that physical exercise enhance beta-cell function in people with diabetes [9] and also in people at high risk of diabetes or prediabetes [10]. However, little is known about how increased physical activity and improved lifestyle habits affect beta-cell function and/or insulin sensitivity in immigrants from Iraq.

These previous findings indicate that a large proportion of the Iraqi population is at risk of developing T2D within the next years. The high prevalence rates of family history of diabetes, obesity and sedentary lifestyle raise the need for a lifestyle intervention targeting individuals at risk of T2D. It is well established that diet- and physical activity-based lifestyle interventions are effective in preventing or delaying the onset of T2D in the short term [11,12] and in the long term [13-16]. However, there are currently no routines or programs to assist health care providers in improving lifestyle in individuals at risk of T2D who come from the Middle East and have a different cultural and socioeconomic background.

Recent studies highlight several obstacles and issues that need to be addressed in order to achieve successful lifestyle change in immigrants from the Middle East. Gender-specific groups must be offered [17]; physical activity sessions should be adapted to the preferences of the participants [18]; successful intervention models should be provided by a multidisciplinary team [18]; and the intervention models should mediate behavioral change and self-empowerment [18]. Therefore, there is a need for a culturally adapted lifestyle intervention targeted to Iraqi immigrants that might differ from conventional lifestyle interventions.

In addition to the challenge of designing a culturally adapted lifestyle intervention, a further challenge remains in the implementation of the lifestyle intervention in community and primary care settings. Every intervention costs resources, but resources are always scarce and informed decision-making is required before implementation of a program at the mass population level. Cost-effectiveness analysis can ensure that limited resources are allocated as efficiently as possible, so that decision makers can take informed decisions based on the benefits outweighing the costs [19]. Although active screening for T2D combined with subsequent lifestyle intervention is cost-effective [20] compared to the “wait and see” or “do nothing” approach that currently prevails, no study has emphasized the cost-effectiveness of culturally adapted lifestyle interventions for high-risk immigrants from Iraq.

## Aim/purpose

Immigrants to Sweden from Iraq are at high risk of developing T2D, but little is known about factors preventing the development of T2D in this group. The aims of the study are to:

(1) Develop a culturally and primary health care-adapted lifestyle intervention program focusing on increased levels of physical activity and healthier eating habits.

(2) Study if the program has an effect on glucose metabolism (measured as fasting glucose level) and whether the change in fasting glucose is depending on insulin sensitivity index (ISI), insulin secretion (measured as oral disposition index (DIo)) and/or family history of diabetes.

(3) Explore factors that can predict beneficial and non-beneficial responses to the lifestyle intervention, such as baseline physical activity, motivational level, attitudes towards lifestyle change and adherence to intervention components.

(4) Study the cost-effectiveness of this lifestyle intervention from short term and long-term time horizon with patient, health care and societal perspectives.

## Methods/design

### Study design

The study is a 6-month randomized controlled lifestyle behavior intervention trial, where intervention and control groups are followed at 3 and 6 months. Written informed consent will be obtained before randomization. Eligible participants not willing to participate will be registered as such.

### Participants

#### Eligibility criteria

Participants are recruited from the MEDIM baseline study that by December 2012 had included 1398 men and women aged 30 to 75 years born in Iraq, and in whom a glucose tolerance test was performed and sociodemography and lifestyle was characterized. In total 40% of the participants are estimated to be at risk of diabetes either by having prediabetes (IFG, IGT or IGR) or by their constellation of risk factors according to FINDRISC scores [21] resulting in a moderate (17%) to high risk (33%) to develop diabetes within the next decade. Thus we will have an eligible population of 1398*0.40 = 560 individuals, of whom 60% or 336 are estimated to finally agree to participate in the study. The participation rate is based on experiences from an intervention study of Arabic women, which had a participation rate of 62% [17]. In the baseline study 315 Iraqi individuals had a moderate risk (i.e. an estimated 10 year incidence rate of diabetes of 17%) [21] and 275 individuals had a high risk (i.e. an estimated 10 year incidence rate of diabetes of 33%) [21]. Based on a mean time of two years from baseline to the start of the study, we estimate that 26 individuals may have developed diabetes during this period. They will consequently be excluded from the study. Based on a drop-out rate of about 16%, we estimate that of the 310 individuals that initially participated 260 will complete the study (130 per group).

Inclusion criteria were being born in Iraq, age 30 to 75 years and high risk of diabetes as measured by

A. IFG, IGT or IGR identified by an oral glucose tolerance, plasma glucose (glc) at fasting (f-glc) and at 2 hours (2-h glc) during glucose tolerance test:

•  IFG: f-glc 6.1-6.9 mmol/L (110.125 mg/dL) and 2-h glc <7.8 mmol/L (<140 mg/dL)

•  IGT: f-glc < 6.1 mmol/L (<110 mg/dL) and 2-h glc 7.8-11.0 mmol/L (140.199 mg/dL)

•  IGR: f-glc . 6.9 mmol/L (.125 mg/dL) and 2-h glc 7.8-11.0 mmol/L (140.199 mg/dL)

B. or by Finish diabetes risc score (FINDRISC) with over 10% risk of diabetes in 10 years.

Exclusion criteria were diabetes, current pregnancy, mental incapability and/or cognitive impairment, current CVD or history of CVD events. CVD includes stroke, angina or myocardial infarction (MI), percutaneous transluminal coronary angioplasty (PTCA), congestive heart failure (CHF), coronary artery bypass graft surgery (CABG), transient ischemic attack (TIA) and peripheral vascular disease (PVD) or other physical disorders that prevent physical exercise.

#### Randomization/blinding

Subjects agreeing to participate will be randomly allocated to the intervention (n = 155) or control group (n = 155). Randomization will be stratified by age, gender, prediabetes and FINDRISC score, with the aim of obtaining an equal distribution of participants between the two groups. Spouses will be randomized to the same group, and spouses not fulfilling the inclusion criteria will be invited to participate in the study by supporting their husband or wife.

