**Figure 1 F1:**
[figure not shown]
Flow chart summary of the 6-month lifestyle intervention study.

Ten group counseling sessions will be provided during a period of 6 months. Each group will contain 16 individuals of the same gender (there will be five groups of men and five groups of women). The sessions target diet, physical activity and behavioral change with the goal of equipping the subjects with the necessary knowledge and skills to gradually achieve permanent behavioral changes. Behavioral change is a model involving *motivation*, *action* and *maintenance*[24]. It supports changes in diet and physical activity and goal-setting, and involves action planning with goals and coping strategies. The intervention group will be supported in their efforts to reach the following goals, which are considered to have preventive effects against diabetes [15,24]: weight reduction of ≥5%, moderate intensity physical activity ≥30 minutes at least 5 days/week, dietary fat <30% of total energy (E%), saturated fat <10 E% and fiber ≥15 g/1000 kcal. The participants will also be encouraged in everyday life to reduce their time spent physically inactive, *e.g.* sitting or lying down, as much as possible. The intervention group will be encouraged to regularly fill in a “smart goal” sheet to help them to specify their goals (such as to lose 0.5 kg per week), and to explain why they want to do it (for example “*I don’t want to get diabetes*”), how they will reach their goals (“*I will walk briskly for 30 minutes every day after work*”) and the coping plan they will apply to conquer different possible obstacles that may appear (“*I will ask my grandmother to come over and babysit while I am away at practice*”), as suggested in the European guidelines to prevent diabetes [24].

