## Statistical analysis

### Sample size and power calculation

#### Fasting glucose

From the baseline study and earlier intervention studies on Arabic participants, we estimate a standard deviation (SD) of fasting glucose of 0.6 [12,63]. Based on earlier studies, we assume that the true difference between the intervention and control group means is 0.22 mmol/L [12,63]. We will be able to reject the null hypothesis that the population means of the intervention and control groups are equal with a power of 0.86.

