### Univariate and multivariate analysis

The trial data will be analyzed on an intention-to-treat basis. Bivariate and multivariate analyses will assess the effects of the intervention (compared to controls) on fasting glucose level, weight, physical activity level and dietary intakes, with adjustment for age and gender, and will identify factors that can predict beneficial and non-beneficial responses to the intervention (*e.g.* baseline physical activity, motivation, attitude, adherence to the intervention). Continuous data will be analyzed with paired Student’s t-tests and linear regression, and categorical variables with chi square tests and logistic regression with 95% confidence intervals.

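### The power figure and planned analysis of fasting glucose treat participants as independent, although the intervention arm is counseled in ten groups and spouses are allocated together; any positive correlation makes the test anti-conservative and lowers power

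*Protocol article*

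**What the plan says.** Two features of the design in the protocol article tie participants together:

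- **Counseling groups.** The Intervention section (text with Figure 1) plans ten sessions over 6 months: "Each group will contain 16 individuals of the same gender (there will be five groups of men and five groups of women". Group counseling sessions adds discussion led by a health coach and/or a nutritionist. Controls get usual care from primary care nurses (Control group), so this grouping exists in one arm only.
- **Couples.** Randomization/blinding states: "Spouses will be randomized to the same group". This applies to both arms. Spouses who do not meet the inclusion criteria may take part as supporters.

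Two statements treat participants as independent:

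- **Power.** Sample size and power calculation, Fasting glucose, gives three figures: "we estimate a standard deviation (SD) of fasting glucose of 0.6", "the true difference between the intervention and control group means is 0.22 mmol/L", and rejection of the hypothesis that "population means of the intervention and control groups are equal with a power of 0.86". It states no n, alpha, ICC or design effect. Eligibility criteria expects 260 completers, 130 per arm, from 310 randomized.
- **Analysis.** Univariate and multivariate analysis states: "Continuous data will be analyzed with paired Student’s t-tests and linear regression". Adjustment is for age and gender. No group term, couple term or clustered variance is named, and clustering is not mentioned anywhere in the article.

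**The concern.** For couples, the unit of randomization is the couple. In the intervention arm, participants also share a coach, sessions and group discussion for 6 months. Either feature can make outcomes within a unit more alike than outcomes across units. Each participant then carries less independent information than the formulas assume.

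If that correlation is positive, the confidence interval for the fasting glucose difference is too narrow, and an ineffective programme has more than a 5% chance of a significant result. The other continuous outcomes are exposed in the same way. The error would also carry into the economic results, because Economic evaluation calculates cost-effectiveness ratios for outcomes that reach statistical significance.

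**Working it through.** **Inputs from the protocol article.** SD 0.6 (unit not given, taken as mmol/L); difference 0.22 mmol/L; 130 completers or 155 randomized per arm; ten counseling groups in the intervention arm, so 130/10 = 13 completers or 155/10 = 15.5 randomized per group.

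**Assumptions, not in the documents.** Two-sided alpha 0.05; group ICC (ρ) 0.01 to 0.05; share of participants in enrolled couples (f) 20 to 50%; within-couple correlation (r) 0.1 to 0.2.

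**Step 1: the plan's own figure.** Under independence, SE = 0.6 × √(2/130) = 0.0744 and 0.22/0.0744 = 2.956, so power = Φ(2.956 − 1.96) = 0.840 (0.838 with the t distribution). This is close to the stated 0.86 but below it; 0.86 needs 138 per arm. With 155 per arm, power is 0.898.

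**Step 2: allow for the correlation.** With m participants per group:

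- Intervention-arm design effect: DE_I = 1 + (m − 1)ρ + f·r
- Control-arm design effect: DE_C = 1 + f·r
- SE = 0.6 × √((DE_I + DE_C)/n)
- Power = Φ(0.22/SE − 1.96)
- Factor k by which the unadjusted SE is too small: √((DE_I + DE_C)/2)
- True alpha of the unadjusted test: 2 × (1 − Φ(1.96/k))

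Worked example (ρ = 0.02, f = 0.3, r = 0.2, n = 130, m = 13): DE_I = 1 + 0.24 + 0.06 = 1.30; DE_C = 1.06; SE = 0.6 × √(2.36/130) = 0.0808; power = Φ(2.721 − 1.96) = 0.777; k = √1.18 = 1.086; true alpha 0.071.

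**Step 3: the range at 130 completers per arm, 13 per group.**

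| Scenario | ρ | f | r | k | Power | True alpha, unadjusted |
|---|---|---|---|---|---|---|
| Independence | 0 | 0 | – | 1.00 | 0.840 | 0.050 |
| Groups only | 0.01 | 0 | – | 1.03 | 0.819 | 0.057 |
| Groups only | 0.02 | 0 | – | 1.06 | 0.798 | 0.064 |
| Groups only | 0.05 | 0 | – | 1.14 | 0.737 | 0.086 |
| Couples only | 0 | 0.2 | 0.1 | 1.01 | 0.833 | 0.052 |
| Couples only | 0 | 0.5 | 0.2 | 1.05 | 0.805 | 0.062 |
| Both, mild | 0.01 | 0.2 | 0.1 | 1.04 | 0.812 | 0.059 |
| Both, middle | 0.02 | 0.3 | 0.2 | 1.09 | 0.777 | 0.071 |
| Both, upper | 0.05 | 0.5 | 0.2 | 1.18 | 0.705 | 0.098 |

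**Step 4: the same if all 155 per arm were analysed, 15.5 per group.** Groups only: 0.876 at ρ = 0.01, 0.855 at 0.02 and 0.790 at 0.05. Both sources: 0.870 (mild), 0.837 (middle) and 0.761 (upper).

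With only ten groups there are few degrees of freedom for the group variance, so these normal-approximation powers are slightly optimistic.

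**The case against.** The case on the other side has five parts, and much of it stands.

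- **The consequences are conditional.** A reader might infer that the standard errors are certainly too small and the power certainly missed. The documents give no ICC, couple share or within-couple correlation, so they do not support certainty. The direction needs positive correlation, which is plausible for a shared household or a shared coach but is not shown. The group ICC may also be modest: exercise is self-selected, goal sheets and prescriptions are individual, and adjusting for gender removes gender differences between the single-sex groups.
- **Spouse allocation looks like the main problem but is not.** Couples alone cost about 1 to 4 points of power in the table. Only couples in which both spouses are eligible and enrolled count. If every participant had a spouse in the source cohort, the article's own rates (40% at risk, 60% agreeing) would give a share of 0.40 × 0.60 = 24% if spouses' eligibility and consent were unrelated. With r = 0.2, power is then about 0.82.
- **Clustering does not explain the whole gap to 0.86.** About 2 points are gone at 130 per arm before any correlation. At 155 per arm, 0.86 is roughly kept up to a group ICC of about 0.02. Against that, the article itself expects only 130 per arm to complete.
- **The variance method could sit in an analysis plan that is not shown.** This is fair as to detail, and linear regression does not exclude clustered standard errors. But the article states its analysis methods and its power, and neither makes an allowance. A later model choice would not add the missing allowance to the stated power.
- **Allocation might be foreseeable for a second spouse.** A reader might infer that one spouse could enrol after the other's arm is known. The article describes no such sequence and requires consent before randomization, so this is not supported.

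**Conclusion.** The concern holds in conditional form. The design fixes two sources of possible correlation, and neither the power statement nor the stated analysis allows for them. The counseling groups are the larger source and couples the smaller.

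Given positive correlation within the assumed ranges, power at 130 completers per arm lies between about 0.81 and 0.70 instead of 0.84, and the unadjusted 5% test has a true error of about 6 to 10%. These figures rest on assumed values of ρ, f and r and on a two-sided 5% test. They do not show that 0.86 is out of reach for every plausible input: with 155 per arm analysed and mild correlation, power is 0.87.

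**What to change.** **Univariate and multivariate analysis.** Analyse fasting glucose and the other continuous outcomes with a partially nested mixed model: a random counseling-group effect in the intervention arm only, and a couple effect or couple-clustered standard errors in both arms. Because groups are single-sex, husband and wife sit in different groups, so the two effects cross. Use small-sample degrees of freedom (Satterthwaite or Kenward-Roger, for example), since there are only ten groups. State that group and couple identifiers will be recorded; the article does not say that they are.

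**Sample size and power calculation, Fasting glucose.** Restate the power with n per arm, alpha, sidedness and a design effect, over a declared range of group ICC, couple share and within-couple correlation.

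**Cost.** A wording change, two identifiers in the data, slightly wider intervals and a less favourable power figure. No extra participants are needed to make the inference valid. The change does not restore lost power: holding groups at 13, reaching 0.86 would take 149 analysed per arm in the mild scenario and 163 in the middle one. Whether the lower power is acceptable is a decision for the trial team to make openly.

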#### Intervention group

The intervention group will be offered (A) regular group sessions led by an Arabic-speaking health coach with a similar ethnic background to the group and (B) free physical activity sessions. Others showed that the willingness to enroll in a diabetes prevention program was predicted by perceived risk of diabetes [22] and before the start of the study we will hold an education session to provided information about how our lifestyle habits influence our health.

#### Control group

Information will be sent to the primary health care center (PHCC) that the participant is at high risk of T2D and that he/she will participate in the study as control. The control group will receive “treatment as usual”, *i.e.* they will be instructed by nurses in the PHCC to increase their physical activity, to reduce their weight and to make the same diet changes as those recommended to the intervention group.

